## Abstract

**Introduction:**

Stroke is a leading cause of adult disability, and the transition from hospital to home can be fraught with challenges. The HOME Rehab trial is designed to address if better health outcomes for stroke survivors can be achieved with a contextually relevant and tailored occupational therapy discharge planning and support intervention. Process evaluations inform clinical trial findings and future scale up, as well as how to implement a successful intervention effectively into policy and practice. This paper describes the protocol we are using in the HOME Rehab process evaluation planning and activities.

**Methods:**

Using a theoretically informed approach, mixed methods are being used to collect data and address all aspects of the RE-AIM framework. Quantitative data will comprise clinician surveys, trial logs and fidelity checklists as well as screening and recruitment numbers. Semi-structured interviews with trial participants and carers and focus groups with occupational therapists will provide qualitative data. A concurrent triangulation approach will be taken to draw on the strengths of multiple methods to cross-validate findings. The RE-AIM framework will be used to interpret the qualitative and quantitative data together as well as highlight areas of convergence or divergence in the findings. Multiple data sources will be integrated to refine the interpretation of outcomes, understand the context of program delivery, and identify key findings. Drawing on, and integrating data from, multiple perspectives and methods will strengthen the overall findings and provided detailed insights into the causal mechanisms as well as the contextual factors that may influence intervention outcomes.

**Discussion:**

Process evaluations can optimize study outcomes by improving how a complex intervention is implemented, informing the actions of policymakers and clinicians. For the HOME Rehab intervention, the process evaluation may provide valuable data necessary to explain the trial findings, as well as inform future scale-up and implementation if the HOME Rehab intervention is shown to be effective.

**Clinical trial registration:**

https://www.anzctr.org.au, identifier ACTRN12618001360202.

## Introduction

1

Globally, stroke is the leading cause of disability in adults and each year millions of stroke survivors must adapt to a life with restrictions in activities of daily living as a consequence (1). Stroke rehabilitation interventions, tested first in clinical trials and then translated into practice, reduce disability after stroke (2). Conducting process evaluations alongside clinical trials, and embedding theoretical frameworks within process evaluations, ensures trials effectively inform stroke policy and practice (3–5), providing vital evidence about how an intervention does or does not work, how an intervention is implemented, its mechanisms of impact, and the contextual factors that impact on the intervention. All of which provides details for scale up and replication in different settings should the program be effective (5).

The United Kingdom Medical Research Council (MRC) recommends that researchers conduct process evaluations alongside clinical trials (6). When implementing complex intervention, such as the HOME Rehab trial (7), process evaluations are particularly useful for understanding multiple interacting components, variable outcomes, and the new behaviors required by the people delivering or receiving the intervention (8). Key domains recommended to be evaluated in a process evaluation within the MRC guidance (context, quality of implementation and mechanisms of the intervention) are often augmented in process evaluations from established evaluation frameworks such as the Reach, Effectiveness, Adoption, Implementation and Maintenance framework (RE-AIM) (9). Together, these guidelines and frameworks seek to enable research translation from clinical trials to clinical practice.

### About the HOME Rehab trial

1.1

The HOME Rehab trial is designed to address if better health outcomes for stroke survivors can be achieved with a contextually relevant and tailored occupational therapy discharge planning and support intervention; the full clinical trial protocol and intervention components has been published elsewhere (7). The HOME Rehab intervention was developed to address the known challenges experienced when transitioning from hospital to home after stroke, with some returning to hospital soon after discharge (10–12). Compared with transitions to nursing homes, transitions to home after stroke are associated with increased risk of readmission or emergency department visits (13), suggesting there are factors in the home environment which likely contribute to a patient’s early readmission. This context is perhaps complicated by the known insufficient communication and service coordination during discharge planning (14–16) with stroke survivors reporting they struggle with independence, social participation and resuming usual activities (17–20). With the numerous contextual factors and the complexity of the HOME Rehab trial (multiple sites, multiple states and health jurisdictions; interacting intervention components; collection of primary and secondary outcomes), conducting a process evaluation nested within the HOME Rehab trial will provide key evaluation data that will support interpretation of effectiveness data. This process evaluation will provide insights into how the intervention either worked or did not, explaining differences in outcome, and gain insights into the experience of both trial participants as well as clinicians working in rehabilitation.

### Objective of the process evaluation

1.2

The overall aim of the process evaluation is therefore to explain the trial findings, as well as inform future scale-up and implementation if the HOME Rehab intervention is shown to be effective. If effective, understandings about implementation of the intervention, its mechanisms of impact, and contextual factors influencing delivery and functioning of the intervention will critically inform evidence-based stroke policy and practice (5).

Therefore, the specific objectives of the HOME Rehab Trial process evaluation are to:describe the characteristics of participating hospitals and participants to assess reach;explore the effects of individual intervention components on the primary outcome of participation;describe the perceived effectiveness of relevant intervention components [including the relationship between the participant and their occupational therapist, the importance of goals set, the in-hospital component (including the pre-discharge visit to the home), the community component (including the General Practitioner (GP) liaison), and staff training] from the participant, carer and occupational therapist perspectives;describe the perceived acceptance of the HOME rehabilitation intervention by involved occupational therapists and how their attitudes may or may not have shifted after training and involvement in the trial;outline the HOME Rehabilitation experimental intervention as delivered in terms of quality, quantity, adaptations and variations (planned and unplanned); andestimate the extent to which intervention delivery is normalized among the intervention healthcare professionals and related practice staff at the completion of the trial.

## Methods and analysis

2

### Design

2.1

The HOME Rehab trial is a multicenter, phase III RCT being conducted in Australia with concealed allocation, blinded measurement and intention-to-treat analysis (7). The setting is in-hospital rehabilitation centers across the states of New South Wales, Queensland, South Australia and Victoria; a list of trial sites is available on the trial registry. The MRC guidelines for process evaluation will provide an overall conceptual framework to evaluate the HOME Rehab trial (5), collating data on context (how context affects implementation and outcomes), implementation (what is implemented and outcomes) and mechanisms of the intervention (how the intervention produces change). These guidelines also emphasize the need to clarify the key causal assumptions made in developing the HOME Rehab intervention, which are outlined in Figure 1. Figure 1 shows these causal assumptions made, how they inform the key functions of the process evaluation, and how this will contribute to interpretation of outcomes from the main trial.

**Figure 1 fig1:**
[figure not shown]
Key functions of the HOME trial process evaluation and relationships amongst them. Blue boxes represent components of process evaluation, which are informed by the causal assumptions of the HOME Rehab experimental intervention, and inform the interpretation of outcomes from the main trial.

Within this mixed method process evaluation, the RE-AIM framework (9) will be applied to understand and describe the reach, effectiveness, adoption, implementation and maintenance of the HOME Rehab intervention. These five domains of the REAIM framework will enable a comprehensive, mixed-methods evaluation, one which will systematically explore implementation of the HOME Rehab intervention in the trial and allow the research team to prepare for ‘real world’ implementation as outlined in the logic model for the process evaluation (Figure 2).

**Figure 2 fig2:**
[figure not shown]
Logic model of the HOME trial process evaluation.

### Process evaluation study population

2.2

The process evaluation has been integrated into the randomised controlled trial (RCT) design of the HOME Rehab trial, and will therefore involve stroke clinicians (occupational therapists) working at participating centers, stroke survivors aged ≥45 years (HOME Rehab Trial participants), carers (of HOME Rehab Trial participants) and HOME Rehab trial occupational therapists.

### Process evaluation methods

2.3

A mix of quantitative and qualitative approaches will therefore be used to address the aims of process evaluation (Table 1). A concurrent triangulation approach will be taken to draw on the strengths of multiple methods to cross-validate findings (21).

**Table 1 tab1:** Quantitative and qualitative methods of process evaluation data collection employed in the evaluation.

Stage of trial	Data collected
Pre-implementation	Records of engagement meetings with staff at participating sites Meetings with occupational therapy managers and rehabilitation physicians to understand service context and service models for discharge planning after first stroke Descriptions of the organizational characteristics of services using face-to-face interviews, observation and notes from site visits Survey of all occupational therapists (beliefs about occupational therapy discharge planning) Participant baseline data across primary and secondary outcomes
Recruitment	Site screening, eligibility and recruitment log (includes reasons for ineligibility or non-participation) to report participant recruitment and retention as per CONSORT. Site bed numbers and average length of stay to report representativeness of site Participant hospital length of stay, age, and stroke severity to report representativeness of participants
Implementation	Intervention provider details (includes expertise, background and specific training provided) to report against TIDieR checklist Fidelity monitoring checklists for all components of the intervention completed at participating sites for each intervention provider annually Diary of co-rehabilitation intervention information (including use of community services, hospital readmission and healthcare resource utilization data from time of discharge to end of 12 months) Intervention documentation per participant, including session number and length, mode of delivery, session goals, activities completed, equipment/materials provided and trial protocol variation records Costs of delivering the intervention Records of meetings with key staff across trial (site coordinators, occupational therapists, consumer engagement panel, trial management committee, data safety and monitoring committee)
Post-intervention	Participant end of intervention (4-weeks post discharge) and follow-up (6-months post discharge) across primary and secondary outcomes Post-intervention readmission and healthcare resource utilization, including pharmaceutical and cost data Caregiver burden at post-intervention (4-weeks post-discharge) and follow-up (6-months) Face-to-face or telephone interviews with participants, carers and occupational therapists who participated in the intervention Survey of all occupational therapists (beliefs about occupational therapy discharge planning) Organizational survey (12-months following final participant recruited) to report maintenance of trial intervention elements

CONSORT, Consolidated Standards of Reporting Trials; TIDieR, Template for Intervention Description and Replication.

To address the ‘reach’ REAIM dimension, the HOME process evaluation will collect data on the characteristics of participating hospitals and participants. The representativeness of participating hospitals and participants will be evaluated against Australian stroke statistics including hospital length of stay and bed numbers; participant age, and stroke severity. Further, we will maintain an audit of trial recruitment log to record the willingness of potential participants to participate in the study. This will provide information on the proportion of eligible/invited potential participants who enrol in trial. Reasons for potential participant’s non-participation will be included from each site’s log.

For the effectiveness dimension, the process evaluation will explore perceptions of the benefits of individual intervention components on the primary outcome of participation. Each intervention component has been outlined in the published protocol (7), allowing the interviewer to qualitatively explore perceived effectiveness of, for example, the pre-discharge visit separately to the goal setting component. To triangulate data and gain detailed understandings, semi-structured interviews with participants and carers, and focus groups with occupational therapists will explore the mechanisms through which the intervention brings change. Knowledge about the mechanism is vital for understanding how and why the intervention is or is not effective and for future replication.

To explore patient and carer perspectives, the trial coordinator will prepare a list of participants from the HOME Rehab trial who have completed their 4-week assessment but are within 12 months of discharge (noting demographics and attributes to facilitate maximum variation sampling). Potential process evaluation participants and carers will then be contacted by phone and invited to participate in a telephone interview. To ensure a range of participants are recruited, variation in sampling will be based on gender, severity of impairment, residential status (living alone/ not alone), study group (control/experimental), and trial site. Patients and carers who agree to an interview will be telephone interviewed by an occupational therapist trained in qualitative interviewing and not involved in delivering trial interventions. At the commencement of the interview, verbal consent to participate with will be audio recorded along with the rest of the interview and sent for professional transcription. Stroke survivor participants and carer interviews will be conducted separately to enable each participant to speak freely about their experience of discharge from rehabilitation and engagement in the trial. The semi-structured interview guide is based on the aims of the trial, process evaluation, and previous process evaluations. The guide was pilot tested and minor changes to the order of questions were made. Semi-structured interviews with approximately 14–16 people with stroke and 10–12 carers from both the experimental and control groups will explore perceptions of discharge planning, transition to home, adherence to self-monitoring, and social support. Additionally, the relationship between the participant and their occupational therapist, perceptions of goal setting and pre and post discharge visits (tailored to study group), sessions with GP involvement (intervention group only) and suggestions for improvement will be explored.

To explore the perspective of trial occupational therapists, focus groups will be held at selected trial sites. Recruitment will aim to obtain data from a sample across the sites with maximum variation in terms of gender, experience, and involvement in the trial. There will be four focus groups with 6–8 therapists in each group and facilitated by an independent researcher. In the focus groups, occupational therapists working within the trial will explore their experiences with discharge planning and the process of delivering the HOME intervention including training, being involved in the trial, implementing the intervention, and the aspects of the trial went well or not so well. Further, adherence to the protocol including implementation barriers and enablers encountered and suggestions for improvement will be explored. Insights gained will provide detailed information to understand the mechanisms of impact of the intervention on the trial outcomes.

To explore ‘adoption’ the process evaluation will describe the perceived acceptance of the HOME intervention by involved occupational therapists and how their attitudes may or may not have shifted after training and involvement in the trial, affecting uptake. A questionnaire will be sent to all trial occupational therapists working in rehabilitation pre-and post-implementation of the intervention. Questions seek to explore occupational therapists’ beliefs about discharge planning and the work they do with inpatient stroke survivors who will be discharged to the community (home environment) at the end of their program. Respondent demographics will be collected and questions will elicit perceptions of discharge planning and patient participation post-discharge. Additionally, pre-discharge occupational therapy home visit practice and beliefs, as well as barriers and enablers of providing discharge planning support to stroke survivors during rehabilitation will be explored. The second questionnaire distributed at the end of the trial will contain additional questions about the HOME trial, including experiences and satisfaction with the trial, perceived impacts, benefits and challenges, and any site-specific issues. The survey is based on the objectives of the trial and process evaluation, as well as previous work. Responses will be rated on a 6-point categorial scale of agreement and obtained through short answer questions. A printed and electronic copy of the questionnaire will be provided to all trial occupational therapists to maximize response rates. Analysis will focus on both perceived acceptance of the intervention and any shifts in beliefs that occur after training and involvement in the HOME Rehab trial.

The ‘implementation’ dimension of the process evaluation aims to describe the HOME rehabilitation intervention as delivered in terms of quality, quantity, adaptations and variations (planned and unplanned). To assess program fidelity to the protocolized intervention and other factors that may impact the outcome, we will audit the trial documentation, training records, fidelity scoring records, and trial protocol variation sheets. Using descriptive statistics to report the findings, these audits will provide insights into how the planned intervention was implemented.

To explore the ‘maintenance’ dimension, we aim to examine the long-term individual and organizational impacts of the intervention and understand the extent to which its delivery was normalized among the healthcare professionals and related practice staff. Twelve months post completion of the trial, the lead investigator will survey each site principal investigator to understand which, if any, elements of the HOME Rehab intervention are used, and if so, how they are integrated into usual discharge planning practices at the site.

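### The maintenance survey is not linked to the pre-trial service records, so elements a site already used could be read as maintained HOME intervention

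*Protocol article*

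**What the plan says.** Section 1.2 of the protocol article lists among its objectives to estimate "the extent to which intervention delivery is normalized among the intervention healthcare professionals" and related staff when the trial ends. Section 2.3 takes this up under the maintenance dimension: "we aim to examine the long-term individual and organizational impacts of the intervention".

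The measure follows directly: "Twelve months post completion of the trial, the lead investigator will survey each site principal investigator" to learn "which, if any, elements of the HOME Rehab intervention are used, and if so, how they are integrated into usual discharge planning practices". The post-intervention row of Table 1 lists the same organizational survey, with the purpose "to report maintenance of trial intervention elements". Neither place mentions use of the elements before the trial.

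Information from before implementation is planned elsewhere. The pre-implementation row of Table 1 has meetings with therapy managers and rehabilitation physicians on "service models for discharge planning after first stroke", and descriptions of each service from interviews, observation and site visits. The therapist questionnaire, sent before and after implementation, covers "pre-discharge occupational therapy home visit practice and beliefs". It is assigned to the adoption dimension.

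**The concern.** The aim is about change caused by the intervention, while the stated measure is a snapshot of practice after the trial. A site that always made pre-discharge home visits and a site that began them because of HOME and kept them would both answer that the element is used. Asking how an element is integrated does not establish when it began.

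The process evaluation is meant to inform scale-up if HOME proves effective. If existing practice is taken for retained intervention, the error runs in one direction: HOME appears to have lasted better than it did. The effect would be greatest for the elements closest to usual care.

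**Working it through.** The article gives no figure to reproduce on this point, so the check sets its statements side by side.

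1. **Aim against measure.** Impact and normalization (sections 1.2 and 2.3) describe a move from earlier practice. The survey (section 2.3 and Table 1) records present use and present integration. No earlier state enters the measure as described.

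2. **Is the earlier state collected?** Yes, in part. Table 1 plans service-model meetings and organizational descriptions before implementation, and the first questionnaire asks about home visit practice.

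3. **Is it brought to the maintenance question?** Not in the text.
   - Section 2.3 directs the questionnaire analysis to acceptance of the intervention and shifts in beliefs, not to change in practice.
   - Section 2.5.1 examines delivery across sites and over the duration of the trial. It gives no before/after comparison for maintenance.
   - Section 2.5.3 promises joint interpretation of all results under RE-AIM in general terms and does not tie the early service descriptions to the later survey.

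4. **Could HOME elements overlap with prior practice?** It is plausible. Section 1.2 names goals and the pre-discharge home visit among the intervention components. Section 2.3 covers "perceptions of goal setting and pre and post discharge visits (tailored to study group") in interviews with both study groups, whereas it restricts the topic of GP sessions to the intervention group. The questionnaire asks therapists about home visit practice before HOME is implemented. These places suggest overlap but do not state it.

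5. **Size.** For one element, let *u* be the share of sites using it at follow-up, and *p* the share using it both before the trial and at follow-up.
   - Newly used and retained = *u* − *p*.
   - If all current use were read as maintained intervention, the overstatement would be *u* − (*u* − *p*) = *p*, with 0 ≤ *p* ≤ *u*.
   - The article gives neither *u* nor *p*, nor the number of elements. The overstatement therefore lies anywhere from nil to the whole of current use.
   - *p* is a joint quantity. It needs each site's before and after status linked, so an overall pre-trial rate would not be enough.

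**The case against.** The strongest reply is that the article never says how the survey will be scored. It contains no count, percentage, definition of maintained or reporting rule, and an answer on how an element is integrated might itself reveal that it was routine beforehand. Survey items and coding rules normally sit in the instrument or the full protocol, which is not shown. Baseline context is planned, and joint interpretation under RE-AIM could bring it in.

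Much of this stands, and it rules out several stronger readings that a reader might infer:

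- *That the plan reports existing practice as maintained intervention.* No reporting rule is stated, so this is a risk, not a described procedure.
- *That baseline information is missing.* It is collected. What is missing is its link to the survey.
- *That usual care already contained HOME elements.* The components are defined in a separate publication. Asking both groups about goals and visits, with questions adapted to the group, does not show that usual care included them.
- *That the scale-up conclusion is biased by a known amount.* Scale-up depends first on effectiveness and draws on every dimension. No decision rule uses maintenance.

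The reply does not remove the core point. The article does state the aim, respondent, timing, question and purpose of the maintenance measure, and that measure cannot by itself answer that aim. A general promise of joint interpretation does not say that each site's later answers will be read against its own earlier practice.

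**Conclusion.** The point holds as a missing link between two planned sources. As described, the maintenance survey cannot distinguish retained intervention from prior practice, and the information that might do so is not directed to it. Any resulting error would overstate maintenance, on the assumption that some HOME elements were in use at some sites beforehand. The documents make this plausible but do not show it, and they give no basis for a size.

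This is a minor improvement to the process evaluation. It has no bearing on the main trial's randomized comparison.

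**What to change.** Before the follow-up survey:

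1. Fix one list of HOME elements and use it in the survey.
2. For each site and element, code pre-trial use as yes, partly, no or unknown from the pre-implementation meeting records, site-visit notes and first-questionnaire home visit items. Whoever codes should not have seen the follow-up answers.
3. Report, per element and site, *newly used and retained* separately from *already in place* and *prior use unknown*. Decide in advance where *partly* belongs, or give it its own line.

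One sentence in section 2.3 under maintenance would state the comparison. Section 2.3 times the survey from completion of the trial, whereas Table 1 times it from recruitment of the final participant. The two should be reconciled so that the coding deadline is clear.

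**Cost.** A short extraction and one table, with no new data collection. There may be many *unknown* entries: the early records are not stated to be element by element, and the questionnaire is answered by individual therapists while the survey goes to site principal investigators. The maintenance figure may come out lower. The table would also not prove that HOME caused a new practice, since sites can change for other reasons. It would only stop prior practice from being credited to the trial.
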